**Figure 4 F4:**
[figure not shown]
**Schematic outline for relating outcome measures to pathophysiological mechanisms**. We expect to identify one or more of the hypothesized etiological mechanisms in each SIS patient. These mechanisms might be related to the reported variations in SIS symptoms, course, and treatment outcome. (MRI = Magnetic Resonance Imaging, X-ray & EMG task = radiographs during EMG recorded abduction and adduction tasks for measurements of acromiohumeral distance, and FoB = 3D kinematics with Flock of Birds system).

The following scenarios are considered:

1) Dynamically reduced subacromial space, due to (relative) cranial translation of the humerus.

Humerus cranialisation causing encroachment of subacromial tissues will be characterized by limited AH in resting state on standard radiographs, further decrease in AH during abduction tasks, and decreased reconstructed subacromial volume (MRI). In some patients, this cranialisation might be (partially) compensated by I) co-activation of arm adductor muscles, and/or II) altered kinematics of the humerus and the scapula (scapulohumoral rhythm). Nevertheless, instead of a compensation mechanism, altered scapulohumeral rhythm can also be a cause of SIS in some patients (e.g. decreased scapula lateral rotation during arm abduction, with consequent relative cranial translation of the humerus). Pain is suspected to be the main trigger for compensation mechanisms. Therefore, we expect that these compensation mechanisms will be less manifest during the second round of experiments, after a subacromial injection with lidocaine.

Particularly relevant positive outcome measures for this subgroup are: decreased AH, low AR (adductor co-activation), altered Principal Action for adductor muscles, decreased reconstructed subacromial volume during active abduction, degeneration of rotator cuff muscles and altered scapulohumeral rhythm.

2a) Statically reduced subacromial space, due to structural narrowing (classic etiology). The subacromial space can be narrowed as a consequence of structural anatomic variations, e.g. a hooked acromion impinging on the subacromial tissues. These potential causes will be investigated and quantified using shoulder radiographs and (segmented) MRI-arthrographies.

As a consequence of structures impinging on the rotator cuff, compensation mechanisms might be present to prevent further subacromial encroachment, including altered scapulohumeral rhythm (increased lateral rotation or increased posterior tilt during arm abduction) and adductor co-activation during arm abduction. Again, we expect that these compensations mechanisms will be less manifest after a subacromial injection with lidocaine.

Important outcome measures for this subgroup are: shape parameters of scapula (hooked acromion, Bigliani classification, acromial spurs) and humerus, the presence and extend of rotator cuff tendinosis (fibrosis, tendinitis, partial articular or bursal side tear).

2b) Statically reduced subacromial space, as a consequence of subacromial inflammatory processes, without signs of actual structural subacromial narrowing.

In some subjects, symptoms of SIS are related to predominantly intrinsic causes. In these patients, we expect to find little or no anatomic variations impinging on the cuff and no evidently decreased AH. The hypothesized disbalance between subacromial volume and the space needed for subacromial structures can be caused by e.g. subacromial oedema, fibrosis, tendinosis and tendinitis, which will be mainly assessed by means of MRI.

As a consequence of the subacromial inflammatory reaction and pain, patients might have an altered scapulohumeral rhythm and adductor co-activation.

Main outcome measures for characterizing this subgroup are: the presence and extend of rotator cuff tendinosis (fibrosis, tendinitis, partial articular or bursal side tear) and subacromial oedema.

2c) Statically reduced subacromial space due to encroachment of subacromial tissues by an adjoining pathology or other structures than the acromion.

Besides humerus cranialisation and the classical etiologic mechanisms that have been related to SIS, subacromial tissues can be impinged as a consequence of an adjoining pathology or other structures than the acromion. For example, coracoid impingement and subacromial osteophytes in (otherwise asymptomatic) osteoarthritis of the acromioclavicular (AC)-joint have been reported as causes for pain with arm abduction. In our study, these causes will be investigated with the use of radiographs, MRI and 3D-kinematics recordings. Therefore, the most important methods of investigation for this subgroup are: MRI and radiographs to evaluate e.g. AC-osteoarthritis and subacromial osteophytes, impingement on the superior aspect of the glenoid, impingement at the outlet of the shoulder, coracoid impingement, and other (subacromial) pathologies or impinging structures causing a deficiency of subacromial space.

3) Combination groups

As with many diagnoses in general, the cause of SIS symptoms is presumably heterogeneous. We expect that in most patients one of the hypothesized mechanisms will play a main role, but in a subgroup of patients, a combination of 2 or more mechanisms will be causing SIS.

Additionally, we expect to identify specific pathologies other than SIS causing shoulder complaints, including cuff tears, calcifying tendinitis, first stage frozen shoulder, and SLAP lesions. Patients with these pathologies will not be included in the current SISTIM study, but some (cuff tears or calcifying tendinitis) will be analyzed separately in distinct research projects (trial registry numbers: NTR1545 and NTR2282).

#### Statistical analyses

Patient data, including patient characteristics, physical examination, interview, radiological findings, questionnaires, psychological scores, biomechanical measurements and MRI findings will be entered in a database.

With regards to presence of cranial translation of the humerus as detected on radiographs during rest and abduction and adduction tasks, statistical analysis will be performed by a means of repeated measures ANOVA, with the measure of co-contraction controlled as a confounding factor.

For the isometric Principal Action EMG measurements, data are tested by means of a General Linear Model analysis for repeated measures, controlling for factors Muscle, subacromial anaesthetics, sAH and VAS for pain.

RoM in standardized motions will be analyzed with a General Linear Model analysis for repeated measures, controlling for factors VAS pain, subacromial anaesthetic, dAH and sAH. dAH obtained from 3D-kinematics will be analyzed equally.

Additionally, we will use students' unpaired t-tests to compare continuous variables (e.g. patient characteristics, clinical scores, RoM, dAH) between defined pathologic subgroups.

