#### Sample size

A combination of techniques will be applied to classify SIS-patients into pathophysiologic subgroups, most of which are newly developed (section 2.3). The acromiohumeral distance (AH) is a recognized parameter related to rotator cuff disease and based on literature it has rather wide inter-individual variations. Therefore, sample size calculation will be based on this parameter.

In a study of Gruber et al., AH values of 9.4 (SD = 3.4) were observed in subjects without diagnosed cuff pathology. A subacromial space narrower than 6 mm on radiographs is considered pathologic and strongly indicative for supraspinatus tendon rupture [46].

The unpaired *t*-test was used to determine the sample size with a difference of AH of 3.4 mm between groups assumed as clinically relevant, comparing AH during abduction task radiographs in patients where humerus cranialisation plays a key-role compared to AH in other subgroups of SIS patients.

Based on the standardized difference: 3.4 mm/3.4 mm = 1.0, a required power of 80% and a p-value of 0.05 for significance, the Altman's Nomogram resulted in 30 shoulders/patients per group.

In our hypothesis, we defined 4 etiological mechanisms. Based on clinical experience and literature, we assume around 30% type III acromion responsible for complaints of SIS,[16] 20-30% of the SIS symptoms are caused by humerus cranialisation and pathologic motion patterns,[47] 15-20% by subacromial inflammatory processes without subacromial narrowing and 5-10% by other impinging structures than the acromion, leaving around 10-30% for a group in which SIS symptoms seem to be caused by two or more hypothesized etiologic mechanisms. With 30 patients needed in the humerus cranialisation subgroup (i.e. 30% of the patients), this leads to a total group size of 100 patients diagnosed with SIS based on patient history, physical examination, radiographs and MRI arthrography.

Additionally, we expect that around at least 25 patients will be diagnosed with another diagnosis than SIS after MRI-arthrography and radiographs [40,48]. These patients can not be included in the SISTIM study but selected patients will be analyzed separately in distinct research projects, if eligible (trial registry numbers:NTR1545 and NTR2282).

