**Figure 3 F3:**
[figure not shown]
**Experimental setup for isometric arm-shoulder force tasks in 24 directions**. The subject has the arm in a splint, which is connected to a force transducer. Subjects must bring the arm force driven red cursor into the blue target area, which indicates force direction (n = 24 directions) and force magnitude. The exerted force, perpendicular to the humerus long axis, is recorded together with EMG to measure the activity of 10 individual shoulder muscles.

The subjects are asked to exert a maximal voluntary force (MVF) in 4 equidistant directions with a maximum of 50 N and maintain this force for 2 s using custom made visual feedback software (Matlab, The MathWorks Inc, Natick, MA, USA). The exerted force and force targets are visualized on a display, expressed in cursor that has to be moved to consecutive targets on a wheel in which the spokes denote force directions and the rim denotes the desired force magnitude (Figure 3). Subjects are subsequently asked to exert 75% of the lowest MVF value onto the force transducer for 2 s in each of 24 equidistant directions that are indicated on the display. The same routine of 24 measurements will be performed 30 min after a subacromial injection with lidocaïne. Muscle activations for 10 muscles around the shoulder are recorded in each of the 24 directions during the 2 sets of measurements.

The direction of maximum activity or Principal Action (PA) for each muscle is determined [22,51] and the Activation Ratio of the abductor and adductor muscles similar to the method described above [58,59]. We expect that pain will influence the Principal Action direction of the muscles [51]. Patients with pain will consequently show an increase in activation of the glenohumeral depressors during arm abduction moments (i.e. adductor co-activation as expressed in low Activation Ratio's). The AR's obtained within this 'Principal Action' set-up will be compared to AR's obtained from the derived abduction and adduction tasks as obtained with the EMG set-up applied during the acquirement of radiographs, taking potential experimental dependencies of AR into account.

The second hypothesis is that after lidocaine injection the muscle activation patterns of the patients move toward a normal activation pattern, as expressed in higher adductor Activation Ratio's and near normal Principal Action directions [5,51].

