## Discussion

Despite the fact that there is no clear consensus on its etiologic mechanisms nor which combination of diagnostic criteria defines SIS, numerous clinical trials exist on patients with the diagnostic label "SIS". Conflicting in- and exclusion criteria for SIS are used across these heterogeneous studies, complicating interpretation of reported results. Additionally, several pathologies that have a similar patient history, pain pattern and findings on physical examination can be mistakenly diagnosed as SIS [45]. Conclusions of these studies are based on results of patients with varying etiologic mechanisms and for that matter even varying pathologies wrongly diagnosed as SIS, resulting in the wide variety on views with respect to aetiology, diagnosis and treatment of SIS that exists nowadays. Instead of studying the outcomes of various treatment modalities in patients with SIS symptoms, first a detailed analysis of possible underlying pathophysiologic mechanisms is needed. In this way, potential subgroups can be identified, subsequently needing specific approaches in both research and clinical decision-making, with regards to diagnostics and treatment pathways.

The SISTIM study is a cross-sectional descriptive large cohort study in which consecutively included patients will undergo a multitude of biomechanical, kinematical and clinical tests. Patients will be selected using strict eligibility criteria, including radiographs and MRI. As a result a unique set of radiological (radiographs combined with EMG, MRI), biomechanical (muscle activation patterns) and 3D motion data (Flock of Birds) will be available on each individual patient, besides usual clinical data and outcome measures (e.g. CS, WORC). This will give better insight in the etiologic mechanisms in patients with symptoms diagnosed as SIS. Whether there is actual encroachment of subacromial tissues is determined by 1) the volume of these tissues and 2) the available subacromial space (static and dynamic). Both are investigated in our study: the status of subacromial tissues will be investigated with MRI, and we will use bony shape parameters, 3D kinematics and muscle activation patterns, to study their role on the subacromial volume of each patient. As this subacromial space is mainly limited by the scapula and humerus, the interaction of (bony) shape parameters and the (dynamic) position of these structures will be investigated as well.

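### The repeated-measures GLM named for the Principal Action EMG data needs, in its standard form, all 20 muscle-by-round values from each patient; a mixed model would keep incomplete patients and some precision

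*Protocol article*

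**What the plan says.** The Statistical analyses section of the protocol article fixes the model for the isometric Principal Action measurements: "data are tested by means of a General Linear Model analysis for repeated measures". The terms of that model include muscle and the anaesthetic, and the article describes the analysis as "controlling for factors Muscle, subacromial anaesthetics, sAH and VAS for pain". Because muscle is a factor, all muscles enter one model.

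The data structure is in the section on EMG muscle activation patterns, in the text under Figure 3: "Muscle activations for 10 muscles around the shoulder are recorded in each of the 24 directions during the 2 sets of measurements". On the second set it says: "The same routine of 24 measurements will be performed 30 min after a subacromial injection with lidocaïne".

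The article gives no expected rate of unusable recordings. The Discussion takes a full data set for granted, saying of the radiological, biomechanical and motion data that they "will be available on each individual patient, besides usual clinical data and outcome measures". The Sample size section makes no allowance for lost recordings when it states that "this leads to a total group size of 100 patients diagnosed with SIS".

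**The concern.** In its usual form, a repeated-measures GLM treats each patient as one row with a value in every within-patient cell. A row with a gap is left out. With 10 muscles and two rounds there are 20 places for a gap, so a small failure rate per channel can become a much larger loss of patients while nearly all recordings are in hand.

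The same form takes one covariate value per patient. VAS pain may well change between a round without lidocaine and a round with it, and the standard layout cannot use such a covariate.

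At stake is the precision of the before/after-lidocaine contrast. That contrast is secondary goal G and the second hypothesis in the EMG section.

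**Working it through.** **Plan's own figure.** The article gives no figure for the EMG model. Its only sample-size figure concerns acromiohumeral distance: 30 patients in a subgroup taken as 30% of the total, and 30 / 0.30 = 100, which reproduces. The 30 per group does not: with "Based on the standardized difference: 3.4 mm/3.4 mm = 1.0, a required power of 80% and a p-value of 0.05 for significance", the two-sample formula gives 16 per group (17 with the exact t-test). That is a separate matter. The 100 is used here only as the number of patients recruited.

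**Inputs from the article.** 10 muscles, 2 rounds, so 10 x 2 = 20 cells per patient; 100 patients.

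**Assumed inputs.** q = chance that a muscle gives no usable value; m = share of patients without a second round. Neither is in the article.

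**Formulas.**
- Complete patients, if a failed channel is lost in both rounds: (1 - m)(1 - q)^10.
- Complete patients, if cells fail independently in each round: (1 - m)(1 - q)^20.
- Share of all cells still observed: (1 - q)(1 - m/2).

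Example for q = 2%, m = 5%: 0.98^10 x 0.95 = 0.776; 0.98^20 x 0.95 = 0.634; 0.98 x 0.975 = 0.955.

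| q | m | Complete, channel lost in both rounds | Complete, cells independent | Cells observed |
|---|---|---|---|---|
| 0.5% | 0 | 95% | 90% | 99.5% |
| 1% | 5% | 86% | 78% | 96.5% |
| 2% | 5% | 78% | 63% | 95.5% |
| 5% | 5% | 57% | 34% | 92.6% |

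At 2% and 5%, about 22 of 100 patients are dropped although about 95% of the cells were observed.

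**Behaviour of the method.** A standard repeated-measures ANOVA routine, given simulated data with one failed channel in one patient, refused to fit because the data were unbalanced. A linear mixed model fitted incomplete data.

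**Cost in precision.** 100 data sets of 100 patients were simulated at q = 2% (both rounds) and m = 5%. The assumed SDs were 0.3 between patients, 0.15 for the patient-specific anaesthetic effect and 0.3 residual. The mixed model had a random intercept and a random anaesthetic effect per patient; some fits warned of an estimate at the boundary.
- Complete-case analysis: 77.6 patients on average, standard error of the anaesthetic effect 0.02286.
- Mixed model: standard error 0.02069.
- Ratio of standard errors: 0.02286 / 0.02069 = 1.105. Ratio of variances: 1.105^2 = 1.22.

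A cross-check gives the same size: about 95 patients have both rounds, and 95 / 77.6 = 1.22. The gain therefore comes almost wholly from patients with a failed channel. A patient without a second round adds little to the before/after contrast in either model.

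**The case against.** The strongest objection is that deletion of incomplete patients is inferred. The article names no procedure, software, data layout or deletion rule, and a long-format fit of a general linear model could keep incomplete patients. Listing VAS pain as a covariate even leaves room for that reading. This stands: the loss follows from the standard form of the named method, not from a statement in the article. The point is still more than a missing-data rule left to an analysis plan that is not shown, because the article does fix the model.

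A reader might infer more in three ways, and the documents do not support any of them.

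- **That the analysed sample will fall far below 100.** No failure rate is given. The lowest figures need 5% failure, independent in each round. The second round follows 30 min after the injection, so a bad channel would more plausibly fail in both.
- **That the lidocaine effect will be biased.** The article does suspect pain as the main trigger of compensation, so losing patients with more pain would matter. But a detached electrode has no evident link to pain. The arm is fully supported, the target is 75% of the patient's own lowest maximal force, and the second round is done under anaesthetic. No bias was calculated, and a mixed model would remove it only if the data are missing at random.
- **That range of motion and dAH lose patients in the same way.** The article names the same type of model there ("RoM in standardized motions will be analyzed with a General Linear Model analysis for repeated measures"), but lists neither muscle nor motion as a factor. If each motion is modelled separately there are two cells per patient, and a missed motion leaves the others intact.

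It is also fair to say that the EMG aims are secondary, in a study that calls itself descriptive, and that the loss of precision in the simulated case is modest.

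**Conclusion.** The point holds for the Principal Action EMG analysis, mainly as a loss of precision. In its standard form the named model uses only patients with all 20 values and cannot use a pain score that differs between rounds. Between 57% and 86% of patients remain under the assumed 5% to 1% loss per muscle (both rounds) with 5% missing the second round; 90% to 95% remain at 0.5% and no missed round. At 2% and 5% the standard error of the anaesthetic effect is roughly 10% larger than it need be. These sizes rest on assumed loss rates, on the usual complete-row fit, and, for the standard error, on the simulated variances. Selection toward patients with less pain is a risk to keep in view, not a demonstrated bias. The change is worth making because it is nearly free, not because the planned analysis would fail.

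**What to change.** In Statistical analyses, replace the repeated-measures GLM for the Principal Action EMG data by a linear mixed model:

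- fixed effects as now planned: muscle, anaesthetic (before, after), sAH and VAS pain, with VAS pain entered per round;
- random effects for patient and patient-by-muscle, and a random anaesthetic effect per patient;
- fitted to all available recordings, with the number of patients and cells used reported;
- the complete-case repeated-measures GLM kept as a sensitivity analysis.

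The section on patient phenotyping lists VAS for daily activities and rest and does not say that it is scored in each round. The text should say whether it is; if not, one extra score per round is needed. Since lidocaine is expected to act through pain, the anaesthetic effect is best also shown without VAS in the model.

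The same type of model may be used for range of motion and dAH for consistency, but no loss has been quantified there.

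Cost: a change of analysis wording and slightly more modelling work. The model relies on data being missing at random, still loses a patient whose sAH is missing, and recovers little about the lidocaine change in a patient who misses the second round.

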#### 3D kinematics and changes in subacromial volume (E, F, G)

Range of Motion (RoM) and 3D motions of forearm, humerus and scapula with respect to the thorax will be recorded by means of an electromagnetic tracking system: 'Flock of Birds' (FoB, Ascension Technology Corp, Burlington, VT, USA) and custom made computer software (FOBVis, Clinical Graphics, Delft, the Netherlands). The FoB obtains 3D kinematical data using sensors on thorax, scapula, humerus, forearm and thorax. After palpatory identifying three dimensional positions of standard bony landmarks of the arm, shoulder and thorax with respect to the sensors for each patient, local bone coordinate systems are created, based on the subject's individual anatomy. The glenohumeral rotation centre is estimated from the position of five scapular bony landmarks using linear regression [61]. The RoM of the following movements is measured: anteflexion, retroflexion, abduction in frontal plane, internal rotation in 0 and 90 degrees of arm abduction and external rotation in 0 and 90° of arm abduction.

3D kinematics and MRI bony segmentation (3D shape parameters of scapula and humerus) will be combined in custom made computer software (Articulus, Clinical Graphics, Delft, the Netherlands) to reconstruct the subacromial space volume and AH during recorded humerus elevations, allowing dynamic measurements of patient-specific subacromial space characteristics [5,62,63]. Additionally, the effect of a subacromial lidocaïne injection on RoM, scapulohumeral rhythm, reconstructed AH and subacromial volume of the affected shoulder will be analyzed.

*Main kinematic outcome parameters*: Passive and active RoM during standardized arm motions (with and without subacromial anaesthetics) of both arms; Scapulohumeral rhythm of affected and healthy arm; Reconstructed changes in AH and subacromial volume during dynamic arm abduction (combining MRI-based shape parameters and 3D RoM measurements).

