#### EMG muscle activation patterns (C, D, G)

We will analyze muscle activation patterns as measured by EMG recordings of 10 shoulder muscles, based on Activation Ratio [58,59] and Principal Action parameters [22,51]. Measurements will be performed before and after a subacromial infiltration of lidocaïne (5 ml, 10 mg/ml), to study potential relations between pain during arm abduction and adductor muscle co-activation and arm-scapula kinematics, respectively.

Subjects are seated with the affected arm in a splint with the upper arm in 45° of internal rotation and the elbow in 90° of flexion. The humerus is positioned in 60° of forward elevation and in 30° of external rotation relative to the transverse plane, Figure 3. The splint is attached to a 3D force transducer which is mounted on a sled so that it can move freely in a direction parallel to the humeral longitudinal axis. The arm is fully supported in order to compensate for gravity. Axial rotation of the humerus is mechanically not restricted to prevent the subjects from generating supplementary moments. In this way, patients can only exert forces perpendicular to the longitudinal axis of the humerus.

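### Lidocaine is always the second measurement round, so its effect cannot be separated from the effect of repeating the tests, yet the plan attributes the change to lidocaine or pain relief

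*Protocol article*

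**What the plan says.** **Order of measurement.** The section on EMG muscle activation patterns says "Measurements will be performed before and after a subacromial infiltration of" lidocaine. After the first set of force tasks, "The same routine of 24 measurements will be performed 30 min after a subacromial injection with lidocaïne". Ten muscles "are recorded in each of the 24 directions during the 2 sets of measurements". The section relating outcome measures to mechanisms treats the lidocaine round as the second round: "these compensation mechanisms will be less manifest during the second round of experiments, after a subacromial injection with lidocaine".

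**Model.** Under Statistical analyses, the EMG data go into a General Linear Model for repeated measures, "controlling for factors Muscle, subacromial anaesthetics, sAH and VAS for pain". The RoM model lists VAS pain, subacromial anaesthetic, dAH and sAH, and dAH is to be analysed in the same way. Neither list contains a round term, and the RoM list contains no term for arm.

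**Interpretation.** Secondary goal G is the effect of the infiltration on RoM, scapular rhythm, reconstructed volume and muscle activation. The second EMG hypothesis reads: "after lidocaine injection the muscle activation patterns of the patients move toward a normal activation pattern, as expressed in higher adductor Activation Ratio's". Scenarios 1 and 2a expect compensation to be less manifest after lidocaine, and scenario 1 names pain as its suspected main trigger.

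**A possible control.** The main kinematic outcomes include "Passive and active RoM during standardized arm motions (with and without subacromial anaesthetics) of both arms". The same section, however, describes the lidocaine analysis for the affected shoulder.

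**The concern.** If the lidocaine round is always the second round, anything that changes because the tests are done twice is counted as lidocaine. Repetition effects are plausible here. The patient steers a force-driven cursor to 24 targets, holding each for 2 s at 75% of the lowest maximal force, with a painful shoulder. Better control on the second attempt could reduce out-of-phase activity and so raise the Activation Ratio (AR), which is the direction predicted for lidocaine. Fatigue could act the other way and hide a real effect.

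At stake is goal G, and with it the argument that adductor co-activation and altered rhythm are pain-driven compensation. A shift due to repetition alone could be reported as release of that compensation.

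**Working it through.** The article states no figure for the lidocaine comparison, so there is none to reproduce. The check has three steps.

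**1. Can the two effects be separated?** Take 100 patients (the planned total in the Sample size section), two rounds each, affected arm only.

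- Patient columns plus anaesthetic: 100 + 1 = 101 columns, rank 101.
- Add a round column: 102 columns, rank still 101. The anaesthetic and round columns are identical, so no choice of model terms separates them.
- Measure both arms in both rounds: 100 patient columns + arm + round + arm-by-round = 103 columns, rank 103. The interaction is now estimable.

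In the both-arm design, the mean change is drift + lidocaine in the affected arm and drift alone in the unaffected arm. The difference is the lidocaine effect if drift is the same in both arms.

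**2. How much could repetition matter? (assumed drifts)** Let the true lidocaine effect be zero and let repetition shift the mean change by δ SDs of the within-patient change. A paired t-test then has non-centrality δ√n, with two-sided α = 0.05.

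| δ (assumed) | δ√100 | False positives, n = 100 | False positives, n = 30 |
|---|---|---|---|
| 0 | 0 | 5% | 5% |
| 0.1 | 1 | 17% | 8% |
| 0.2 | 2 | 51% | 19% |
| 0.3 | 3 | 84% | 36% |

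The n = 100 entries for non-zero drift come from the non-central t distribution (0.168, 0.508, 0.844); simulation gave 17%, 51% and 85%. The n = 30 entries are simulated and show only how the rate depends on n.

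**3. Does VAS in the model remove the problem?** Regress the change in outcome on the change in VAS; the intercept is the anaesthetic coefficient. Assume a VAS change of mean −2 and SD 1.5, no effect of VAS on the outcome, and a drift of 0.3 SD.

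- Variance of the intercept ≈ 1/100 + (−2)²/(99 × 1.5²) = 0.0100 + 0.0180 = 0.0280, so SE ≈ 0.167, against 1/√100 = 0.100 without VAS.
- The simulated coefficient was 0.30, so the drift is still there in full.
- 0.30/0.167 ≈ 1.8, and rejection fell to 42%.

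VAS lowers the rejection rate by widening the standard error. It does not remove the bias. The article does not say whether VAS is recorded again in the second round. A VAS value taken once per patient would not differ between rounds and could not separate them.

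**The case against.** Several objections have force.

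- **The model is described briefly.** A reader might infer that it holds only an anaesthetic main effect averaged over ten muscles, which would dilute an adductor-only effect. The article does not say that. It neither states nor excludes interactions, and it defines the EMG outcomes as muscle-specific. The aliasing does not depend on this, because an interaction with anaesthetic is equally an interaction with round.
- **Non-adductors as a drift control.** It is tempting to treat the change in non-adductors as session drift and subtract it. The documents do not support that. The EMG section expects pain to influence the Principal Action of the muscles generally, so non-adductors may respond to lidocaine. AR is bounded by 1 and is close to 1 in normally acting muscles, so those muscles have less room to rise than co-activating adductors. Practice may also reduce adductor co-activation specifically.
- **Design features that limit drift.** If a muscle's EMG level is scaled by k in both phases, (kA_IP − kA_OP)/(kA_IP + kA_OP) leaves AR unchanged. The tasks are submaximal and short, and the second set comes 30 min after injection. This limits gain drift and fatigue but does not exclude practice or a change in co-activation.
- **Assumed magnitudes.** The drifts are assumptions, and the 17%, 51% and 84% come from a test without VAS. They illustrate sensitivity and do not predict an error rate.
- **Weight.** Goal G is one of ten secondary goals in a descriptive study. This stands and limits the importance of the point.

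**Conclusion.** The point holds in this form: the order is fixed, the anaesthetic factor alone marks the round, and the before/after change in the affected arm cannot be attributed to lidocaine or pain relief as the article does. This is a matter of design, and no later choice of model terms for the affected arm alone can undo it. It rests only on the described order and the listed factors.

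The size and direction of any repetition effect are unknown. Under the assumed drifts, a false lidocaine effect at n = 100 ranges from about 17% to 84% without VAS, and is about 42% at 0.3 SD with VAS under the assumed VAS changes.

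A reader might infer that the expected lidocaine effects are spurious, or that the subgroup classification is compromised. Neither follows. A true effect may well exist; it is simply not identified. The measures listed for assigning subgroups do not include the response to lidocaine, and the sample size rests on acromiohumeral distance (AH) between subgroups.

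**What to change.** - **(a) RoM and, where recorded in both rounds, scapulohumeral rhythm.** Add arm (affected/unaffected) to the model under Statistical analyses and take the arm-by-round interaction as the lidocaine effect, using the both-arm recordings that the kinematic outcome list can be read to include. Confirm that the unaffected arm is recorded in both rounds. If it is not, a few minutes of repeat recording are needed; without them, (b) applies. The cost is some precision: with equal variances, the variance of the difference in changes is 2σ²(1 − ρ), so its SD is √2 ≈ 1.4 times the one-arm SD at between-arm correlation ρ = 0 and equal to it at ρ = 0.5. The contrast also assumes similar drift in both arms, so it reduces the confounding and does not guarantee its removal.
- **(b) EMG (AR, Principal Action) and reconstructed AH and subacromial volume.** These have no second-arm control. Report the result as a change in the second round, after injection, and do not attribute it to lidocaine or pain relief alone. Reword goal G, the second EMG hypothesis and scenarios 1 and 2a accordingly. This costs wording only.
- **(c) Adductor hypothesis.** State an adductor-specific before/after contrast on AR so that the test matches the hypothesis, interpreted as in (b). Do not use the change in non-adductors as an estimate of session drift. The planned recordings suffice.
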